#### Data preparation and statistical analysis

The data that will be collected will consist of information relating to medical history, mood, scores on cognitive tasks and blood samples. All data, including blood samples will be de-identified. Codes for the depletion (ATD) and sham depletion (BAL) will be held in an envelope in a securely locked space in the unlikely event of an emergency that requires the code to be broken. Only researchers on the listed research team will have access to the final dataset.

To examine changes in response to ATD (mood, cognitive parameters and tasks, amino acid concentrations, etc.) as well as after treatment (mood symptoms, cognition, SSRI monitoring) a series of repeated measures ANOVAs will be conducted with time (baseline, ATD administration and 12 weeks into treatment) and challenge procedure (ATD/BAL administration) as within-subject factors. We will also evaluate for a significant effect of relevant baseline amino acid levels on the observed changes. If such a significant interaction is discovered, ANCOVAs will be performed with baseline values as covariates.

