### Study objectives and hypotheses

The first objective of this study is to investigate the effects of ATD as a physiologically induced short-term central nervous serotonergic deficit on mood in adolescents with MDD (Phase A of the study) prior to open label treatment initiation with SSRI fluoxetine (Phase B of the study). We expect that, in Phase A, ATD will have dysfunctional effects on mood, emotional face recognition, aspects of reversal learning, and attention-related cognitive parameters as assessed within a testing battery, when compared to a balanced control condition. Such results would reflect a 5-HT sensitivity to ATD with regards to the aforementioned parameters relevant for depression [16, 17], and would be in line with the findings amongst the adult population [10, 18–20].

The second objective of this study is to determine if the effects of ATD on mood as a physiological 5-HT-related neurochemical and dietary challenge procedure predicts treatment response to SSRI administration after a period of 12 weeks of open label pharmacological treatment with fluoxetine (Phase B). We hypothesise that the effects of ATD administration on mood from Phase A will predict clinical improvement relating to depressive symptoms and overall depressive symptomatology 12 weeks into SSRI treatment (Phase B). Specifically, we hypothesise that ATD may be indicative of serotonergic vulnerability in relation to symptoms relevant for adolescent depression.

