## Expected outcomes

### Mood

We expect that ATD-induced mood changes (Phase A) when compared to baseline and BAL administration will be inversely related to the mood-based treatment response to fluoxetine (as assessed via the POMS) and improvements in depressive symptomatology (BDI, HDRS, CDRS-R) 12 weeks into treatment (Phase B). In particular, our assumption is that symptom severity at baseline and change in mood following the ATD challenge will be proportional to mood change due to fluoxetine treatment as response to ATD may be an index of serotonergic vulnerability for mood changes.

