## Discussion

This study may identify a new, simple dietary method to predict treatment response, leading to more targeted pharmacological treatment of adolescents with MDD, and may result in a more rapid treatment response. Children and adolescents may tolerate the ATD/BAL amino acid mixtures better than adults. There have been no serious side effects or complications reported in the studies conducted in minors [12–14, 39]. This study may identify a new, simple dietary method to predict SSRI-related treatment response in terms of serotonergic vulnerability, possibly leading to more targeted pharmacological treatment of adolescents with MDD. In turn, this may lead to a more rapid treatment response and better outcomes. Consequently, adolescents would be able to return to their prior level of functioning earlier, decreasing the overall burden of disease for the individual and allow better integration into the community. Such an approach needs to be confirmed by future larger-scale studies.

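### The stated ANOVAs and conditional ANCOVA compare mean changes, so they cannot test whether a participant's ATD mood response predicts fluoxetine outcome; the 0.97 power does not cover that objective either

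*Protocol article*

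**What the plan says.** **Objective.** Study objectives and hypotheses states: "The second objective of this study is to determine if the effects of ATD on mood" predict treatment response after 12 weeks of open-label fluoxetine. The matching hypothesis is: "We hypothesise that the effects of ATD administration on mood from Phase A will predict clinical improvement". Under Expected outcomes, the Mood section gives the expected form of the relation: "change in mood following the ATD challenge will be proportional to mood change due to fluoxetine treatment". That section measures the ATD response against both baseline and the balanced control (BAL). It lists POMS, BDI, HDRS and CDRS-R as week-12 outcomes.

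**Analysis.** Data preparation and statistical analysis covers changes in response to ATD and changes after treatment in one sentence: "a series of repeated measures ANOVAs will be conducted with time" (levels: baseline, ATD administration, week 12) "and challenge procedure (ATD/BAL administration) as within-subject factors". If baseline amino acid levels prove to matter, ANCOVAs with baseline values as covariates follow. No other model is named there.

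**Power.** Power analysis gives 0.97 for N = 20, effect size 0.4, two-tailed alpha 0.05 and critical F = 3.26. It labels this as an ANOVA effect for within-subjects factors and calls the calculation preliminary.

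**The concern.** Prediction here is a between-person question: do participants whose mood falls more under ATD improve more, or less, by week 12? A repeated measures ANOVA with time and challenge as within-subject factors asks whether average mood differs between occasions or challenges. A large average ATD effect and a large average improvement can coexist with no relation between the two, and a strong relation can exist with no average change.

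Two things are at stake. Following the section as written leaves the second objective without a result. A significant time effect might also be mistaken for evidence of prediction. If the model is chosen only after the data are seen, there are four outcome scales and many POMS readings to choose from, and at N = 20 such a choice would carry little weight.

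**Working it through.** **1. What the stated models contain.** The ANOVA terms are time, challenge and their interaction. The ANCOVA adds baseline values. The participant's ATD mood change appears in neither as a predictor of the week-12 outcome. In addition, the week-12 level of time has no separate ATD and BAL values, so the two factors do not fully cross.

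**2. Reproducing the 0.97.** Stated inputs: N = 20, effect size 0.4 (read as Cohen's f), alpha 0.05, critical F = 3.26. Inferred inputs, because they return the stated figures: m = 3 measurements, k = 2 groups, correlation between measurements 0.5, sphericity.
- Noncentrality = f² × N × m / (1 − 0.5) = 0.16 × 20 × 3 / 0.5 = 19.2
- df1 = m − 1 = 2; df2 = (N − k)(m − 1) = 18 × 2 = 36
- Critical F(2, 36) = 3.259; power = 0.972

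The figure is therefore the power to detect a difference in means over a three-level within-subject factor.

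**3. Do the two tests answer the same question?** Simulation: N = 20, 2,000 runs, three occasions. The changes from baseline at ATD and at week 12 each have SD 1.

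| Mean changes (ATD, week 12) | True correlation of changes | ANOVA time test rejects | Correlation test rejects |
|---|---|---|---|
| 0, 0 | −0.6 | 8% | 84% |
| 0, 0 | +0.6 | 5% | 83% |
| 0.5, −0.8 | 0 | 98% | 6% |

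The ANOVA is close to its nominal 5% when prediction is real but means do not move. It is almost always significant when means move and there is no prediction.

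**4. What N = 20 gives for the prediction question.** The protocol states no correlation, so a range is assumed. The test is t = r√(18 / (1 − r²)), two-sided 0.05, bivariate normal data.

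| True r | Power |
|---|---|
| 0.3 | 0.25 |
| 0.4 | 0.43 |
| 0.5 | 0.64 |
| 0.58 | 0.80 |
| 0.72 | 0.97 |

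Precision at an observed r of 0.5, by Fisher z: atanh(0.5) = 0.549; SE = 1/√17 = 0.243; 0.549 ± 1.96 × 0.243 = 0.074 to 1.025; back-transformed, 0.07 to 0.77.

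**5. Effect of adjusting for baseline.** The figures in step 4 are for an unadjusted correlation. Suppose the baseline score is independent of the ATD response and correlates 0.5 with the week-12 score (both assumed). Simulated power at r = 0.5 then rises from 0.64 to about 0.77.

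**The case against.** **The section may be a summary.** The article condenses Protocol Version 11, and an analysis plan may exist; neither is shown. Other sections mention analyses that the statistical section omits: allowance for concurrent psychological treatment, and preliminary dose–response relationships involving predictors of response. A reader might infer that the trial has no prediction model anywhere. The documents do not support that. What stands is narrower: the article does assign a method to the ATD and post-treatment data, and that method does not fit its second objective.

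**ANOVA is not the only model.** Correct, since a conditional ANCOVA is also named. Its covariates are baseline values, so prediction remains untested.

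**The power paragraph does not claim to cover prediction.** This is also right. A reader might infer that the protocol asserts 97% power for objective 2, because it gives one figure and ties replacement of those lost to follow-up to it. But the text labels the figure a within-subjects ANOVA effect and goes on to discuss mood effects after ATD. The figure simply does not extend to objective 2.

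**Prediction is not the main hypothesis.** The abstract gives the effect of ATD on mood and cognition as the major hypothesis and prediction as an additional one. The study is called a pilot, and the Discussion asks for confirmation in larger studies. This lowers the severity. Even so, the Discussion presents prediction as the study's promise ("This study may identify a new, simple dietary method to predict SSRI-related treatment response in terms of serotonergic vulnerability"), so the objective needs an analysis that addresses it.

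**Conclusion.** The point holds as a mismatch between a stated objective and the stated method. The named analyses test mean changes, contain no term for the individual ATD mood response, and so give no answer to objective 2. The 0.97 is correct for a within-subject mean effect under the inferred settings and does not describe objective 2.

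For that objective, N = 20 supports estimation more than testing: unadjusted power is 0.25 to 0.64 for r between 0.3 and 0.5. These values rest on an assumed range for r and on bivariate normality. The 80% threshold of |r| about 0.58 might be read as the limit of a baseline-adjusted model too. It is not, because that model's power depends on how strongly baseline predicts outcome, which the protocol does not give.

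This should be fixed, but it does not undermine the trial. The randomised comparison of ATD with BAL in Phase A is unaffected.

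**What to change.** - **Add a model for objective 2.** Regress the week-12 score on each participant's ATD-induced POMS change relative to baseline and BAL, adjusted for the pre-fluoxetine score of the same scale. Name one depression scale as the main outcome, keep POMS as a second outcome, as the Mood section intends, and say how the repeated POMS readings are summarised. Report the slope with its 95% CI.
- **Limit the power statement.** Say that the 0.97 applies to the within-subject effect only.
- **Label objective 2 as exploratory estimation.** As a guide to what N = 20 can show, quote the unadjusted figure (80% power only from |r| of about 0.58) and identify it as unadjusted.
- **Word the conclusion to fit the design.** Phase B has no comparator, so an association could reflect general prognosis. Describe it as prediction of outcome during open-label fluoxetine.

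The cost is one added model and some rewording. All the variables are already collected: POMS on both study days, and POMS and the depression scales weekly in Phase B. The model should be fixed before the outcome data are examined.

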ATD is a neurodietary method used to lower brain 5-HT synthesis, and works on the premise that the essential amino acid tryptophan (TRP) is the physiological precursor of brain 5-HT synthesis. As brain 5-HT can only be synthesised through the availability of TRP in the central nervous system, the consumption of foods or beverages lacking in TRP leads to a respective decline in central nervous 5-HT synthesis. ATD involves the administration of an amino acid mixture lacking in TRP after an overnight protein fast. The administered amino acids compete with endogenous TRP on the uptake into the central nervous system over the blood–brain barrier, which leads to decreased substrate availability for central nervous 5-HT synthesis for a period of several (usually 5–7) hours. Additionally, the administered amino acids stimulate protein synthesis in the liver, which takes TRP from plasma stores and also contributes to depletion (for a detailed review, see Dingerkus et al. [8]).

ATD has been shown to decrease mood in depressed adults in remission, particularly those using antidepressants, but not in healthy controls [9]. Mood response to ATD reliably predicted depressive episodes during a follow-up year [10]. Additionally, ATD reversed antidepressant-induced remission in a large proportion of a study sample involving adults with depressive symptoms [11]. Given its history of temporarily reversing remission amongst treated depressed adults, it may be that ATD is particularly potent amongst those who are responsive to SSRIs.

The impact of ATD on mood has only been investigated in adults, mostly because safe and effective ATD methods targeting central nervous 5-HT synthesis in young people were only recently demonstrated [12–14]. In order to make ATD suitable for use in young people, it must account for body weight. A body weight-adapted ATD procedure, called Moja-De, has been validated in rodents [15] and humans [8], but has never been used to investigate mood-related antidepressant treatment response in adolescents with MDD.

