#### Phase A

Phase A will consist of two separate study days, where participants will be randomised to either receive the ATD (i.e. an amino acid beverage lacking TRP) or BAL (which will consist of an ATD-based amino beverage plus TRP). Each study day will be separated by a maximum of 7 days. For each study day of Phase A, participants will be required to undertake a drug and pregnancy screen (if female), will be administered the respective amino acid challenge beverages (ATD and BAL), and a series of psychological and cognitive assessments (see below). A total of seven blood samples will also be taken per study day in phase A. The type of assessments and rationale for the blood samples are further described below in more detail.

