##### Biochemical assessments and psychological and cognitive tasks to be conducted in Phase A

Several assessments and cognitive tasks will be conducted in Phase A, as outlined in Fig. 1. Assessments include the sampling of blood, mood assessments and cognitive testing.

The primary purpose of the blood samples collected at the beginning of Phase A is to assess baseline levels of TRP and other amino acids. The blood samples that will be collected during the two study days will allow measurement of the relevant amino acids contributing to the depletion. At the beginning of each study day in Phase A, participants will be required to complete the Beck Depression Inventory II (BDI-II) [25], the Hamilton Depression Rating Scale (HDRS) [26] and the Children’s Depression Rating Scale – Revised (CDRS-R) [27]. On the first study day, parents or caregivers will also complete the Child Behaviour Checklist [28]. Mood will be monitored on the two study days through the use of the Profile of Mood States (POMS) after ATD or BAL administration, in 30-min time intervals [29].

Cognitive assessments that will be conducted in Phase A include the Tests for Attentional Performance (TAP, PSYTEST, Herzogenrath, Germany) [30]. The TAP subtests that will be used include Alertness, Working Memory, Divided Attention and Sustained Attention. Between each test there will be a break of approximately 10 min. The Facial Expression Recognition Task will also be conducted on each study day of Phase A [31], as well as a Reversal Learning Task [32].

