#### Trial management

This trial will be managed by the Centre & Discipline of Child and Adolescent Psychiatry, Psychosomatics and Psychotherapy and the Bentley Mental Health Service. The trial will employ several measures to ensure participant safety.

During Phase A, participants will consume the dietary protein amino acid serotonin depletion mixture (ATD challenge). This mixture may cause nausea and vomiting. Additionally, ATD is expected to decrease mood between 5 and 7 h (at maximum). To minimise associated risks with lowered mood, individuals with active suicidal ideation or plans will not be recruited to the study. A study doctor will be available at all times during Phase A to assess and manage these symptoms. Participants will be closely supervised and mood will be monitored frequently on the study days to identify those at risk. Mood will be formally assessed once per hour over 7 hours for each study day (Phase A). Tryptophan replacement (re-feeding) will be given at the end of each study day to normalise substrate availability for 5-HT synthesis. A thorough psychiatric assessment (i.e. mental state, risk assessment and management plan) will be conducted at the beginning and at the end of each study day to clear participants for discharge. The following day, participants will attend a clinical review by a study doctor to assess mood and risk. There will also be close monitoring in Phase B of the study, where participants will be reviewed by the study psychiatrists on a weekly basis for 12 weeks.

Any risk that emerges during the study (i.e. during Phase A or Phase B) will be managed by the research coordinator, who will liaise with the participant’s parent or guardian and arrange for prompt assessment by the participant’s study doctor or the nearest emergency department. All participants will have the research coordinator’s phone number, who will be available during working hours and after-hours of Phase A of the study, and during working hours of Phase B of the study. All participants will be given the Acute Response Team contact details for emergency after-hours support, which is an emergency community-based service that is available 24 h per day. The Acute Response Team will have been briefed about the rationale of this study and will also be regularly informed with regards to the number of participants involved at any point in time. Participants will be provided with a diary card with all relevant contact numbers.

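### The Phase A ANOVA gives the whole challenge day one time level, although mood and amino acids are measured serially, so the within-day course cannot be shown and the ATD–BAL mood contrast may be diluted

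*Protocol article*

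**What the plan says.** The section on data preparation and statistical analysis states the purpose, "To examine changes in response to ATD (mood, cognitive parameters and tasks, amino acid concentrations, etc", and then the model: repeated measures ANOVAs "with time (baseline, ATD administration and 12 weeks into treatment) and challenge procedure (ATD/BAL administration) as within-subject factors". Time has three levels, and only the middle one falls on a challenge day.

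The data behind that level are serial:
- **Mood:** the Phase A assessment section has it monitored "through the use of the Profile of Mood States (POMS) after ATD or BAL administration, in 30-min time intervals". The trial management section gives another frequency: "Mood will be formally assessed once per hour over 7 hours for each study day (Phase A".
- **Blood:** the Phase A section says "A total of seven blood samples will also be taken per study day in phase A".

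The effect is described as time-limited. The Background has reduced substrate for serotonin synthesis "for a period of several (usually 5–7) hours". Trial management says "ATD is expected to decrease mood between 5 and 7 h (at maximum".

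The article does not say which reading, window, mean, peak or area under the curve supplies the challenge-day value. The mood section under Expected outcomes describes the Phase A mood change, which is to predict response to fluoxetine, only as a change compared with baseline and BAL.

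**The concern.** A repeated measures ANOVA takes one value per participant per cell. With one challenge-day level, about 7 or 14 mood readings and seven blood samples must each become a single number, and no term remains for the course within the day. For amino acids, that course is the evidence that depletion happened and when. For mood, the ATD–BAL contrast is the first objective and the same effect is the proposed predictor in the second. If the single number mixes readings taken during the effect with readings taken outside it, the group contrast and the differences between participants both shrink. If the reduction is chosen after the data are seen, the result depends on that choice, in a study of 20 participants.

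**Working it through.** **1. Does the sample-size basis use the same structure?** Inputs from the power analysis section: N = 20, effect size 0.4, α = 0.05, critical F = 3.26, power 0.97. Assumed, because not stated: effect size is Cohen's f, correlation ρ = 0.5, sphericity, g = 2 groups (such as the two challenge orders). For m repeated measurements:

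- λ = f²·N·m/(1 − ρ), df1 = m − 1, df2 = (N − g)(m − 1)
- m = 3: λ = 0.16 × 20 × 3/0.5 = 19.2; df = 2 and 36; critical F = 3.259; power = 0.972
- m = 2, 7 and 14: critical F = 4.41, 2.18 and 1.76

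The stated figures reproduce with three measurements. With g = 1 the critical F is 3.245 and with g = 3 it is 3.276, so the match to two decimals needs g = 2. None of the other measurement counts tried (2, 4, 6, 7, 8, 14, 15) comes near 3.26 for g = 1 to 4. The sample size therefore agrees with a three-level time factor without a within-day profile.

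**2. What can the reduction to one value cost?** The article gives no effect size per reading and no correlation, so this is an illustration. Assumptions: 14 half-hourly readings at 0.5, 1.0, …, 7.0 h; n = 20; paired two-sided 5% test; ATD–BAL difference at its peak of 0.8 SD of the paired difference at one reading; correlation r = 0.7 between paired differences within a day.

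For a mean of k readings that keeps a share s of the peak effect:

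- d = 0.8·s / √(r + (1 − r)/k)
- Day mean, k = 14: √(0.7 + 0.3/14) = √0.721 = 0.849
- Window at 5.0–7.0 h, k = 5: √(0.7 + 0.3/5) = √0.760 = 0.872
- Power from the noncentral t with 19 df and noncentrality d·√20

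| Assumed time course | Day mean: s | d | power | 5–7 h window: s | d | power |
|---|---|---|---|---|---|---|
| Only at hours 5–7 | 5/14 = 0.357 | 0.336 | 0.30 | 1 | 0.918 | 0.97 |
| Linear build-up to 7 h | 0.536 | 0.505 | 0.57 | 0.857 | 0.787 | 0.92 |
| Immediate, lasts 5 h | 10/14 = 0.714 | 0.673 | 0.81 | 1/5 = 0.2 | 0.184 | 0.12 |
| Immediate, lasts 6 h | 12/14 = 0.857 | 0.807 | 0.93 | 3/5 = 0.6 | 0.551 | 0.65 |
| Immediate, lasts 7 h | 1 | 0.942 | 0.98 | 1 | 0.918 | 0.97 |

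For r between 0.5 and 0.9, the day-mean power in the first row runs from 0.38 to 0.25.

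**3. Does the mood schedule matter?** With hourly readings (k = 7) and an effect only at hours 5–7, s = 3/7 = 0.429, d = 0.8 × 0.429/√(0.7 + 0.3/7) = 0.398, and day-mean power is 0.39 instead of 0.30. The conclusion stays, but the readings available differ between the two stated schedules.

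**The case against.** The strongest reply is that the harm comes from reductions the article never states. A peak, an in-window reading or a well-chosen window mean would fit the single level and could lose little. The article condenses Protocol Version 11, and the choice of within-day summary is often left to the full protocol or the analysis plan. This stands to the extent that no loss of power can be asserted. It does not remove the point: the article fixes the time levels, and its sample size agrees with them. A summary defined elsewhere would have to fit that one level, and a within-day time term would contradict it.

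A reader might infer that the level is the moment of the drink, so that the effect is missed altogether. The documents do not support this. POMS is scheduled after intake, and the same sentence uses administration as the name of the condition, not a clock time.

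A reader might also take the 0.30 as the expected power. That rests on reading the trial management sentence as a window at hours 5–7. The Background gives a duration, and the words about a maximum fit a duration too. On that reading the day mean has power 0.81–0.98.

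It can also be said that the sentence is only a condensed summary, since it covers SSRI monitoring and a 12-week level that has no ATD or BAL version. That is true, and it supports separating Phase A from the 12-week analysis. One level per challenge day may suffice for the cognitive tasks, which are described only as done on each study day.

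Finally, the article does not say that the Phase B predictor comes from this ANOVA. Dilution of the predictor follows only if the same reduction is used.

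**Conclusion.** The point holds as a badly fixed model with a conditional consequence. For mood and amino acids, the stated ANOVA has one challenge-day level and no within-day time term; it cannot show the course of depletion or mood and relies on an undefined reduction. The ATD–BAL mood contrast may be diluted. Under the assumptions above, day-mean power ranges from 0.30 to 0.98 according to the timing of the effect, and the power of a 5–7 h window ranges from 0.12 to 0.97. Neither is safe without a stated basis. The documents do not show that the effect will be missed. This should be changed before unblinding. No figure is available for a loss on the amino acid side; there the point is only that one level cannot display a profile from seven samples.

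**What to change.** 1. Analyse Phase A separately from the 12-week outcome. For mood and amino acids, use a repeated-measures mixed model with challenge, scheduled within-day time and challenge-by-time, with the pre-drink value as baseline where one is taken.
2. Before unblinding, fix one ATD-minus-BAL mood summary, such as an area under the curve or the mean over a window, justified in advance from the expected time course. An area over the whole day with evenly spaced readings behaves like the day mean and carries the same dilution. Do not take the window from tryptophan pooled over both conditions: BAL adds 0.7 g of tryptophan per 10 kg, so pooling mixes depleted and loaded profiles.
3. Use the same summary as each participant's predictor in Phase B.
4. Reconcile the 30-minute mood schedule in the Phase A assessment section with the hourly one under trial management, as they determine which readings exist.

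The readings are already planned, so the analysis change needs no new data. The cost is slightly more analysis work and commitment to one summary in advance, which can prove a poor choice if the time course differs from expectation. The challenge-by-time model limits that risk because it shows the whole profile.
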